**Outcome variables.**

**Primary Outcomes:**

- Quality of life. The Functional Assessment of Cancer Therapy-Breast (FACT-B) will be used to measure multidimensional QOL (physical, social, emotional, functional, and breast cancer specific). The FACT-B is widely used in the U.S. and validated in Chinese samples, with satisfactory internal reliability (.90) in Chinese immigrant cancer survivors. The primary outcome of quality of life will be indicated by the total score of the four dimensions including physical, social, emotional, and functional. This will allow for comparison with other studies of cancer survivors.

**Secondary Outcomes:**

- Medical appointments for cancer-related morbidities will include appointments for non-routine cancer-related problems (e.g., lymphedema, breast symptoms, or possible recurrence) but exclude scheduled check-ups and non-routine medical appointments for other problems, such as flu symptoms. Following established procedure, we will ask participants to prospectively record cancer-related medical visits and reasons for the visits 1 month before the 6 week, 6- and 12-month follow-ups. A previous study found that rate of agreement of patients' reports and medical records was 92%, supporting the accuracy of patient reporting. These medical appointments will be coded as a function of reason for the visit (i.e., routine and non-routine cancer-related and non-cancer-related appointments) by raters unaware of participants' conditional assignment. Non-routine cancer-related visits will be verified through medical records and counted as medical appointments for cancer-related morbidities. We have successfully obtained and verified medical records among Chinese BCSs in prior studies. Perceived stress. The Perceived Stress Scale is a psychological instrument widely used for measuring the perception of stress. Its 4 items measure the degree to which situations in one's life are appraised as stressful, with good internal reliabilities (0.76–0.80) among Chinese immigrant cancer survivors.

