Intervention materials will be delivered to participants electronically (email) or through the mail, depending on participants' preferences. Participants who choose the electronic option will receive emails that contain a personalized link to the writing tasks on REDCap. Participants who choose the mail option will receive the writing instructions by mail. There will be an option to switch between the online and mail submission methods and vice versa. Hardcopies will be provided to participants as a default if REDCap is unavailable. All the participants will receive reminders through email or text throughout the intervention, for example, "this is (researcher's name) from the 'My Journey' Study at The University of Texas MD Anderson Cancer Center. This is a friendly reminder that you have 3 surveys left for the study."

Participants in the control condition will be asked to write about facts regarding their cancer diagnosis and treatment in the first two sessions and about their diet, exercise, and sleep habits in the third session. These writing instructions engaged participants, and the control and intervention instructions yielded similar lengths of essays in preliminary study 2. Participants in the self-regulation condition will be asked to write about stress and coping, emotional disclosure, and benefit finding. During session 1, participants will be asked to write about the stress of having cancer and their strategies for coping with cancer-associated stressors. During session 2, participants will be asked to write about their deepest feelings regarding their breast cancer experience. During session 3, participants will be asked to write about positive thoughts and feelings regarding their breast cancer experience. Participants in the self-cultivation condition will be asked to write about how they have strengthened their relationships with others in session 1, how they have grown personally in session 2, and detailing their gratitude towards others or their experience to help others in session 3. The writing instructions were developed based on preliminary study 3 and the community's input. All writing instructions are in Appendix B. Following established procedures, we will ask participants to return completed essays to our research team. In our pilot studies, participants were comfortable sharing their essays. The essays will be used for qualitative data analysis.

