Nearly all of the standardized questionnaires in the study have been validated in Chinese samples with good internal reliability. Questionnaires are provided in Appendix A. Table 1 shows the assessment schedule. Primary outcome, secondary outcomes, mediators, moderators, and clinical information (e.g., medical appointments, cancer recurrence, treatment type, cancer stage, time since diagnosis) will be self-reported at

| TABLE 1. Constructs, Measures, and Assessment Schedule |                 |                                                         |           |      |       |        |
|--------------------------------------------------------|-----------------|---------------------------------------------------------|-----------|------|-------|--------|
| Role                                                   | Construct       | Measures                                                | Base-line | 6 WK | 6 MTH | 12 MTH |
| Primary outcome                                        | Quality of life | Functional Assessment of Cancer Therapy-Breast (FACT-B) | x         |      | x     | x      |

2020-0708: Writing to Heal: A Culturally Based Brief Expressive Writing Intervention for Chinese Immigrant Breast Cancer Survivors

|                   |                           |                                                                  |                                                                                                             |   |   |   |   |
|-------------------|---------------------------|------------------------------------------------------------------|-------------------------------------------------------------------------------------------------------------|---|---|---|---|
| Secondary outcome |                           | Medical appointments for cancer-related morbidities  | Prospectively recorded medical appointments for non-routine cancer-related problems (e.g., breast symptoms) |   | x | x | x |
|                   |                           | Perceived stress                                                 | Perceived Stress Scale (PSS)                                                                                | x | x | x | x |
|                   |                           | Fear of cancer recurrence                                        | FACT21                                                                                                      | x | x | x | x |

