| Mood Check        |                           | Writing Manipulation Check                                       | Writing Manipulation Check                                                                                  |   | x |   |   |
| Covariates        |                           | Demographic information                                          | Race/ethnicity, age, education, income, occupation                                                          | x |   |   |   |
|                   |                           | Clinical information                                             | Age at diagnosis, time at diagnosis, cancer stage, treatment                                                | x |   |   |   |
|                   |                           | Clinical update                                                  | Cancer recurrence                                                                                           | x |   | x | x |

baseline and 6- and 12-month follow-ups. Clinical information will also be obtained through medical records with patients' consent, a procedure successfully used in pilot studies.

Moderating variables and demographics will be self-reported at baseline. Potential psychosocial mediators will be self-reported at baseline and at the 6-week and 6-month follow-ups. The three assessments of mediators will allow for inference of mechanisms in longitudinal models. We will assess biomarkers at baseline and 6-week follow-up, based on the literature. We will also assess self-reported perceived stress at the 6-week follow-up so that objective and subjective measures of stress are expected to be collected at the same time. The Global Mood and Life Satisfaction Sliders will be used at baseline and after each writing session to measure mood. Writing Manipulation Check will be used after completing three writing sessions.

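### The visit log asks for cancer-related visits, but the masked raters' scheme also sorts non-cancer-related ones, and no stated step recovers a visit that was never logged

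*Protocol*

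**What the plan says.** Four statements in section 6.0 of the protocol govern how this outcome is ascertained.

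- **Logging.** Under Secondary Outcomes, "we will ask participants to prospectively record cancer-related medical visits and reasons for the visits", in the month before the 6-week, 6-month and 12-month follow-ups.
- **Table 1.** The same measure is described more narrowly: "Prospectively recorded medical appointments for non-routine cancer-related problems (e.g., breast symptoms".
- **Coding.** The recorded appointments are then "coded as a function of reason for the visit (i.e., routine and non-routine cancer-related and non-cancer-related appointments) by raters unaware of participants' conditional assignment".
- **Verification.** "Non-routine cancer-related visits will be verified through medical records and counted as medical appointments for cancer-related morbidities".

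After Table 1 the protocol adds: "Clinical information will also be obtained through medical records with patients' consent". Medical appointments are among its examples of clinical information. In support of self-report it cites a previous study in which the "rate of agreement of patients' reports and medical records was 92"%.

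Section 4.0 names medical appointments as a secondary outcome, and hypothesis 1.1 in section 2.0 includes them at 6 and 12 months. Under Aim 1 in section 7.0, every analysis other than the primary contrasts is tested at an unadjusted two-sided 0.05 and read as hypothesis-generating.

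**The concern.** The logging instruction and the coding scheme presuppose different logs. A log confined to cancer-related visits leaves little for a non-cancer-related category beyond entries the woman herself mislabelled. A scheme with that category makes most sense if the log is broader. Table 1 gives a third, narrower description.

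The order of the steps matters because masked coding is there to keep classification independent of assignment. If the participant has already decided which visits count as cancer-related, the masked step works on a list filtered by her judgement.

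The writing content differs by arm (section 5.0, Intervention). "Participants in the control condition will be asked to write about facts regarding their cancer diagnosis and treatment in the first two sessions". Self-regulation participants write about cancer stress, feelings and benefit finding. Self-cultivation participants write about relationships, growth, and gratitude or helping others. The trial expects writing to change how women think about their illness: cognitive appraisal, intrusive thoughts and cancer-related identity are all measured as exploratory mediators. A difference between arms in the tendency to put a symptom down to cancer is therefore conceivable. It would change the logged count without any change in visits.

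**Working it through.** No figure in the protocol depends on this point, so there is none to reproduce. The first part is a reading of the steps; the second is an illustration on stated assumptions.

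**Which steps can recover an unlogged visit**

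| Step | Acts on | Can remove or reclassify an entry | Stated to add a missing visit |
|---|---|---|---|
| Participant log | visits described as cancer-related | not applicable | not applicable |
| Masked coding | the logged appointments | yes | no |
| Record verification | visits classed as non-routine and cancer-related | yes | no |
| General record retrieval | clinical information, appointments as an example | not stated for this outcome | no |

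The 92% agreement comes from a previous study and is not given by arm, so it cannot exclude omissions that differ between arms.

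**Size of a possible distortion**

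The protocol gives no visit rate and no logging rate by arm, so every percentage here is an assumption. With equal true visit rates,

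apparent rate ratio = share logged in the intervention arm / share logged in control.

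For 70-80% in an intervention arm and 85-90% in control:

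- lowest: 0.70 / 0.90 = 0.78
- highest: 0.80 / 0.85 = 0.94
- reversed direction, for example 85% against 70%: 0.85 / 0.70 = 1.21
- equal logging at any level: 1

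**Chance of a false significant result**

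Inputs: 64 per arm (section 7.0, Power analysis: 80 enrolled, 20% attrition), two-sided 0.05, equal true rate λ per woman, Poisson counts, normal approximation. Control logging is set at 92%, which borrows the cited agreement figure only as a convenient value. With control share p_c and intervention share p_i,

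z = λ(p_c − p_i) / √[λ(p_c + p_i) / 64], and P = Φ(z − 1.96) + Φ(−z − 1.96).

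Worked case, λ = 1 and p_i = 0.75: z = 0.17 / √(1.67 / 64) = 1.05, so P = 0.18.

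| Intervention logging | Apparent ratio | λ = 0.3 | λ = 1 | λ = 2 |
|---|---|---|---|---|
| 92% | 1.00 | 0.05 | 0.05 | 0.05 |
| 85% | 0.92 | 0.06 | 0.07 | 0.09 |
| 75% | 0.82 | 0.09 | 0.18 | 0.32 |
| 65% | 0.71 | 0.16 | 0.41 | 0.68 |

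Under-logging that is equal in all arms does not move the ratio or the error rate. Only a difference between arms does.

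**The case against.** The case on the other side is substantial.

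- **The restriction is inferred.** A reader might conclude that women are told to log only the visits they judge cancer-related. The protocol does not use the word only, and the raters' non-cancer-related category points towards a broader log. The questionnaires are in Appendix A, which is not at hand, so the wording a participant sees is unknown. This stands. What remains is that the logging instruction, Table 1 and the coding scheme do not agree.
- **Participants are partly masked.** A reader might call the attribution unblinded. Section 5.0 (Blinding) says participants are not told of control and intervention conditions, the study title is neutral, and debriefing follows the last follow-up. A woman knows what she wrote but not her arm's role. This stands, although content could shift attribution without that knowledge.
- **Differential attribution is not documented.** Nothing in the protocol shows that three 30-minute sessions alter symptom attribution, or that any change lasts to the 6- and 12-month windows. Control participants also write about their cancer in two of three sessions. The protocol's examples (lymphedema, breast symptoms, possible recurrence) are problems a survivor would readily link to her cancer. This stands: the mechanism is plausible only, and its direction is unknown.
- **Records are used.** They verify visits and supply clinical information. This answers over-reporting. It does not answer omission, because no passage says records are searched for unlogged visits or that such visits join the count.

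**Conclusion.** The point holds as a mismatch between what is logged and what is coded, together with the lack of any stated step that recovers an unlogged visit. That part rests on the text alone.

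The bias is conditional. It needs logging that differs by arm, for which the protocol offers no evidence of size or direction. Under the assumed 70-80% against 85-90%, the apparent rate ratio would be 0.78-0.94 with no true effect. Under equal logging it would be 1.

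A reader might go further and infer that masking is defeated, or that any observed difference in appointments would be mere relabelling. The documents support neither: masked coding still protects the classification of every logged visit, and differential logging is only a possibility.

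The consequence is confined to one named secondary outcome in hypothesis 1.1, analysed as hypothesis-generating. The primary quality-of-life comparisons are unaffected. The correction is worth making because it is cheap and visits never logged may not be recoverable in the analysis.

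**What to change.** In the Secondary Outcomes text, in Table 1 and on the 6-week, 6-month and 12-month forms, ask participants to record all medical visits in the window with the reason for each. State that the masked raters alone decide which visits are non-routine and cancer-related. This fits the coding categories already written and takes the participant's attribution out of the selection step.

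An alternative is to keep the present instruction and state that medical records are searched for unlogged visits in the same windows in all arms.

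The cost of the first option is a sentence in the protocol, matching wording in Table 1 and on three forms, and a few more entries for participants to write and raters to code.

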**Exploratory outcomes include several psychological health and symptoms.**

- Fear of cancer recurrence will be measured by one item, "I worry that my cancer will come back." It has been found to be one of the items best representing the concept of fear of recurrence. On a 5-point Likert scale (0 as not at all, 1 as a little bit, 2 as somewhat, 3 as quite a lot, 4 as very much), a higher score indicates higher fear of recurrence.
- Spirituality. The Functional Assessment of Chronic Illness Therapy-Spiritual Well-Being (FACIT-Sp-12) is a 5-item questionnaire that measures spiritual well-being in people with cancer and other chronic illnesses.

- Sleep: The Pittsburgh Sleep Quality Index (PSQI) is a self-rated questionnaire assessing sleep quality and disturbances over a 1-month time period. Nineteen individual items generate 4 component scores, of which the sum yields a global score.
- Fatigue will be measured using the PROMIS SF v1.0 – Fatigue 4a. Total scores for scale range from 4 to 20, with higher scores indicating greater fatigue. The internal consistency for the PROMIS SF-Fatigue 4a is .90 or higher.
- Biomarkers. Following the recommended procedure of assessing stress biomarkers in RCTs, stress-related biomarkers (salivary cortisol and alpha-amylase) will be assessed via saliva samples collected four times per day over two consecutive days before and after the intervention. Salivary cortisol and alpha-amylase levels will be assessed at study entry and at the 6-week follow-up four times a day, starting 20 minutes after waking up in the morning, 1200, 1700, and 2100 hours on each of two consecutive days. Following established procedures, patients will be given detailed instructions on collecting their own saliva on their own. Patients will be asked to refrain from eating, chewing gum, exercising, smoking, brushing teeth, and drinking anything except water *for 1 hour before sampling*; and to complete questions (see Appendix A) regarding comorbid conditions (e.g., autoimmune disorders) and medications that may influence cortisol or alpha-amylase levels (e.g., prednisone, dexamethasone, and other steroids) during the sampling period. They will be given a medical bottle equipped with a Medication Event Monitoring Systems Cap (AARDEX Group, Belgium^65), an electronic device that has been shown to reliably track the time a saliva sample is taken. Patients will be asked to mail their samples to our laboratory soon after collection. Retuning the sample within 5 days is a general guideline based on the feasibility and sample quality. However, it is acceptable for the participants to mail the saliva samples within 2 - 4 weeks, because salivary cortisol is stable at room temperature for 2-4 weeks, and alpha-amylase has been shown to be stable under a range of conditions. These procedures for saliva sample collection are routinely used in the field. ENREF 98 The samples will be stored in our laboratory at -20 °C until they are delivered in a large number to be analyzed at Dresden Lab Service, a well-established biochemical assay laboratory headed by [name], in Germany, to be analyzed. Research personnel will be responsible for the transmission of saliva samples. *The saliva sampling procedures were shown to be feasible and successful* in our study involving 155 Chinese immigrant BCSs, of whom 146 (94.2%) provided at least 14 valid samples of the 16 saliva samples at baseline and 6 weeks later. Participants *did not find the procedure*, including fasting for 1 hour before sampling and mailing saliva samples, *to be burdensome*.

**Moderating variables.** Acculturation and enculturation will be measured using the Stephenson Multigroup Acculturation Scale. Acculturation toward the dominant American culture will be measured using the Dominant Society Immersion subscale, which has 5 items and good internal reliability ( $\alpha=0.86$ ), and enculturation toward the heritage culture will be measured using the Ethnic Society Immersion Subscale, which has 5 items and good internal reliability ( $\alpha=0.9$ ). Furthermore, potential moderators such as time of diagnosis, age, age of migration will be self-reported at baseline.

Additional exploratory moderating variables include the following:

- Avoidance will be measured using avoidance subscale of the Impact of Event Scale (IES), which has good internal reliability ( $\alpha=0.77$ ).

- Maintain Harmony will be measured using the maintain harmony subscale of the Brief Collectivism Questionnaire, which was developed to assess general collectivism in Asian culture, while capturing its diverse attitudinal and behavioral manifestations. It has 3 items and good internal reliability ( $\alpha=0.73$ ).
- Collectivism and emotional control will be measured using the collectivism (3 items) and emotional control (3 items) subscales of the Asian American Values scale, which has good internal reliabilities ( $\alpha=0.82-0.92$  for collectivism subscale and  $\alpha=.79 - .84$ ).
- Ambivalence over emotional expression will be measured using the Ambivalence over Emotional Expressivity Questionnaire, which has 5 items and good reliability ( $\alpha=0.80$ ).

**Mediating variables.**

- Posttraumatic growth will be measured using the Posttraumatic Growth Inventory, which assesses perceived positive changes as a result of a specific traumatic event and has good internal reliability ( $\alpha=0.93$ ) and validity in Chinese cancer survivors.
- Self-stigma will be measured using a modified version of the 4-item Self-Stigma Scale-Short Form^79 with good reliability ( $\alpha \geq 0.90$ ). It assesses the internalized prejudices and negative feelings individuals have toward themselves due to having breast cancer.
- Harmony will be measured using self-developed harmony scale, which assess participants' perceived agreement of ideas, feelings, and actions with other. It consists of 4 subscales: affective (3 items), behavioral (2 items), cognitive (2 items), and interpersonal relationships (5 items).
- Gratitude will be measured using Gratitude Questionnaire – Six Item Form (GQ-6), which has six items that measure span, frequency, intensity and density of gratitude and primarily focuses on the unidimensional emotional component of gratitude. It has good internal reliability ( $\alpha=0.87$ ).

